## **9.2 Data handling and source document identification**

All trial data for each patient will be recorded from the source documents onto a pre-designed case report form (CRF) by a trained investigator, adhering to the following rules. All data should be legibly entered in black or blue-black ink using a ballpoint pen in regular script. In the event of an error, it should be crossed out with a single line to ensure the original entry remains legible. The correct entry should then be inserted clearly, and the alterations must be initialed and dated by the person making the correction. Rewriting or the use of correction fluid is not permitted. Participants must not be identified in the CRF by name or admission number. Instead, appropriate coded identification must be used in accordance with study-specific standard operating procedures.

## **9.3 Record keeping and archiving**

The principal investigator (PI) is responsible for the secure archiving of trial documents and databases. All study-specific data and documents must be archived for a minimum of 10 years following the termination of the study. The data will be retained to facilitate potential additional retrospective subgroup analyses or long-term follow-up studies.

# **10 SAFETY**

## **10.1 Definitions of safety outcomes**

Safety outcomes included adverse events, including intolerance to TMS, and severe adverse events. The common adverse effects of TMS include dizziness, headache, tinnitus, and tingling or burning sensation on the scalp, which usually ease spontaneously without symptomatic treatment. Any uncomfortable condition due to the iTBS stimulation and needs to be eased by down-regulating stimulus intensity or discontinuation of stimulation are seen as intolerance. Rare adverse effect of TMS includes seizures, for which physicians will administer appropriate symptomatic treatment.

A Serious Adverse Event (SAE) is defined as any event that:

- requires inpatient treatment not envisioned in the protocol or extends a current hospital stay;
- results in permanent or significant incapacity or disability;
- is life-threatening or results in death;
- causes a congenital anomaly or birth defect.

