## **10.2 Recording and reporting**

Intolerance conditions, as well as seizures, will be dealt with by down-regulating the stimulus intensity, termination of stimulation, or symptomatic management if necessary. During the intervention phase of the study, all SAEs that cannot be excluded as being related to the intervention and intolerance conditions will be collected, fully

investigated, and documented in source documents and CRFs. It is not expected that SAEs related to the intervention will occur after the intervention. In addition, all such events will be reported to the PI and the Data and Safety Monitoring Board (DSMB) as soon as possible (within 24 hours). The DSMB will closely monitor all SAEs for any relationship to the study procedures and protocol and will submit all SAEs to the independent statistician for review.

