### **11.2 Rules for withdrawal of participants**

The participation of individuals in either group should be discontinued if any of the following occur:

- SAEs, as determined by the DSMB, are deemed to be probably related to the trial protocol.
- The investigator believes that it is in the subject's best interest to withdraw from the trial.
- The legal representative of the patient chooses to withdraw consent for participation in the study.

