## 7 SAFETY ANALYSIS

The primary analysis will be the ITT principle between the assigned treatment groups. The proportion of SAEs between the two groups will be analyzed via generalized estimating equations.  $P < 0.05$  will be statistically significant. Statistical analyses will be performed using the R software (version R4.3.0)

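### A seizure treated as the protocol foresees, with no longer stay, disability or threat to life, is not clearly an SAE, is not assured of reaching the DSMB, and falls outside the SAE-only comparison

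*Supplement*

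**What the plan says.** Protocol V2.0 section 10.1, repeated in SAP V2.0 section 2.2.4, sets three categories: adverse events, intolerance to TMS within them, and serious events.

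- **Seizure.** "Rare adverse effect of TMS includes seizures, for which physicians will administer appropriate symptomatic treatment".
- **SAE list.** An event qualifies if it "requires inpatient treatment not envisioned in the protocol or extends a current hospital stay", if it "results in permanent or significant incapacity or disability", if it "is life-threatening or results in death", or if it causes a congenital anomaly. Seizure is not named, and there is no limb for other medically important events.
- **Intolerance.** An uncomfortable condition caused by iTBS that "needs to be eased by down-regulating stimulus intensity or discontinuation of stimulation are seen as intolerance".

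Protocol section 10.2 first says how intolerance and, as a separate item, seizures are handled. It then limits collection to SAEs whose relation to the intervention cannot be ruled out, and to intolerance. Of those it says that "all such events will be reported to the PI and the Data and Safety Monitoring Board (DSMB) as soon as possible (within 24 hours").

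On the uses of these data, one withdrawal trigger in section 11.2 is that "SAEs, as determined by the DSMB, are deemed to be probably related to the trial protocol", and SAP section 7 specifies a single safety comparison: "The proportion of SAEs between the two groups will be analyzed via generalized estimating equations".

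**The concern.** Seizure is the one rare harm that the protocol singles out. Every patient is meant to receive iTBS, every patient has a brain injury, and section 6.1 excludes only seizures that are uncontrolled or amount to status epilepticus. The common effects listed (dizziness, headache, tinnitus, scalp sensations) are subjective, and patients in a vegetative state can hardly report them. Seizure is the named harm that staff can see for themselves.

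Yet the plan gives it no settled status. Foreseeing its treatment can be read as taking it out of the first SAE limb, and the reporting sentence does not mention it. A site could follow the text exactly, send nothing to the board and contribute zero to the SAE comparison after a treated, resolved seizure. The trial could then report no SAE difference between conditions with stimulation-related seizures outside the count.

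**Working it through.** The plan gives no figure to reproduce. The check is to take seizures of differing course through the definitions (10.1), the collection and reporting rule (10.2) and the comparison (SAP 7), reading each literally.

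| Course of the seizure | SAE under 10.1? | Intolerance under 10.1? | 24-hour report to PI and DSMB under 10.2? | In the SAP 7 comparison? |
|---|---|---|---|---|
| (a) Treated as foreseen; stay not extended; not disabling or life-threatening; stimulation neither reduced nor stopped | Not clearly: limb 1 is in doubt because the treatment is foreseen, and no other limb applies | No: no change of stimulation | Not required by the visible text | No |
| (b) As (a), but stimulation reduced or stopped | As (a) | Arguable: fits the definition, though 10.2 lists seizures apart from intolerance | Yes, if classed as intolerance | No |
| (c) Extends the stay, or is disabling, life-threatening or fatal | Yes | Not needed | Yes, if a relation to the intervention cannot be excluded | Yes |

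**Step 1, the definition.** Limb 1 has two routes. The extended-stay route fails in (a) and (b) by construction. The inpatient-treatment route depends on whether the protocol envisioned the treatment, and the paragraph just before it does so for seizures. The remaining limbs need disability, a threat to life, death or a congenital anomaly. An inpatient treated and recovered the same day need meet none of them.

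**Step 2, the reporting rule.** The handling sentence in 10.2 has two subjects, intolerance and seizures. The collection sentence also has two, possibly related SAEs and intolerance. Seizures have dropped out, and the DSMB sentence refers back to what is collected.

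**Step 3, downstream uses.** The DSMB-based trigger in 11.2 and the comparison in SAP 7 both act on SAEs. Classing a seizure as intolerance, as in (b), can mend the reporting but not the analysis. The SAP specifies no table of adverse events, intolerance or seizures.

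**Illustration of scale.** The documents give no seizure rate, so the per-patient risk p is assumed. With n = 44 planned patients (protocol 13.1), P(at least one seizure) = 1 − (1 − p)^n:

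- p = 1%: 1 − 0.99^44 = 0.357
- p = 2%: 1 − 0.98^44 = 0.589
- p = 5%: 1 − 0.95^44 = 0.895

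The planned 15% dropout could leave some sham-first patients without their iTBS period. If all of it fell before iTBS, about 37 patients would be exposed (44 × 0.85 = 37.4), giving 0.311, 0.526 and 0.850. These are chances of any seizure, of course (a), (b) or (c), not of an unreported one.

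**The case against.** A reader might infer that a treated seizure can be neither an SAE nor intolerance, and that the board would be unaware of seizures while patients went on being stimulated. The documents do not support that, for five reasons.

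1. A seizure of course (c) is an SAE whatever treatment was foreseen.
2. Section 10.2 gives seizures the same handling (lower intensity or termination) that defines intolerance. A seizure of course (b) can therefore be read as intolerance and so as reportable within 24 hours.
3. The reference in limb 1 to what the protocol envisions can also mean inpatient care outside the planned study stay, without exempting every complication that the protocol mentions.
4. Section 14.1 makes the DSMB responsible for investigating adverse events, not only SAEs. Section 12.3, on the DSMB, was not available in the text reviewed and may say what the board receives.
5. Other safeguards exist. Under 14.3 the PI reviews abnormal data, CRFs and SAEs after every four randomized patients, and under 11.2 the investigator may withdraw a patient in that patient's interest without any SAE.

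It can also be said that the 5% rate sits poorly with the protocol's description of seizure as rare.

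All of this narrows the point, and some of it stands outright: board blindness is not established. It does not remove the point. Section 14.1 speaks of a reported adverse event without obliging the site to report one. The second reading of limb 1 shows that the wording is ambiguous, not that it is safe. The periodic PI review is neither a 24-hour report nor a report to the board. Nothing in the objection brings a seizure of course (a) or (b) into the comparison, unless the second reading of limb 1 is adopted and makes it an SAE.

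**Conclusion.** The point holds in a limited form. For a seizure that is treated as foreseen, does not prolong the stay and is neither disabling nor life-threatening:

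- SAE status is unclear.
- DSMB notification is not assured by the visible text, unless stimulation is reduced or stopped and the event is classed as intolerance.
- Unless it is classed as an SAE, it is outside the only safety comparison specified. This is the firmer half, because it holds even when the event is reported as intolerance.

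The conclusion rests on the literal wording of 10.1, 10.2 and SAP 7, and on section 12.3 containing no seizure rule; the sponsor should check that section. No size can be put on the number of seizures missed. The probabilities of about 36%, 59% and 90% rest on assumed rates and show only that at least one seizure in the trial is plausible. The plan should be amended on this point, because the gap concerns a named harm and closes with little effort.

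**What to change.** - **Protocol 10.2:** name seizure explicitly among the events collected and sent to the PI and DSMB within 24 hours.
- **Protocol 10.1 and SAP 2.2.4:** add a limb for other medically important events, or make seizure an event of special interest. State that foreseeing seizure treatment in the protocol does not exempt a seizure from the first SAE limb.
- **SAP 7:** tabulate seizures and intolerance by the condition received (iTBS, washout, sham), beside the existing SAE comparison.
- **Consistency:** reconcile 10.1, 10.2, 11.2 and 14.1, and check 12.3, so that the status of a seizure is the same in collection, board reporting and analysis. What follows clinically after a seizure is for the sponsor and the DSMB to decide.

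The cost is amendment wording, with the ethics approval that section 15.2 requires for any amendment, and one table. No new visits, staff or procedures are needed. The downside is a few more expedited reports and possibly a higher reported SAE count.

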## **10.2 Recording and reporting**

Intolerance conditions, as well as seizures, will be dealt with by down-regulating the stimulus intensity, termination of stimulation, or symptomatic management if necessary. During the intervention phase of the study, all SAEs that cannot be excluded as being related to the intervention and intolerance conditions will be collected, fully

investigated, and documented in source documents and CRFs. It is not expected that SAEs related to the intervention will occur after the intervention. In addition, all such events will be reported to the PI and the Data and Safety Monitoring Board (DSMB) as soon as possible (within 24 hours). The DSMB will closely monitor all SAEs for any relationship to the study procedures and protocol and will submit all SAEs to the independent statistician for review.

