## **14 QUALITY ASSURANCE AND CONTROL**

### **14.1 Independent oversight organization**

The DSMB is responsible for assessing clinical care, investigating AEs, and determining whether a reported AE relates to the intervention and is relevant to the trial. The members of the DSMB will not be directly involved in the trial.

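### Protocol 10.2 collects less than the stated safety outcomes, and SAP 7 does not clearly define an iTBS-versus-sham safety comparison

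*Supplement*

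**What the plan says.** **Outcomes.** Protocol V2.0, section 10.1: "Safety outcomes included adverse events, including intolerance to TMS, and severe adverse events". SAP V2.0, section 2.2.4, says the same. Both list common TMS effects, such as headache, dizziness and scalp sensations, and expect most to settle untreated. Both define intolerance as discomfort caused by iTBS that calls for lower intensity or for stopping. Neither limits the outcome to related events.

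**Collection.** Protocol 10.2: "During the intervention phase of the study", "all SAEs that cannot be excluded as being related to the intervention and intolerance conditions will be collected". On later events it says: "It is not expected that SAEs related to the intervention will occur after the intervention". Section 10.3 applies the same causality condition to the follow-up of SAEs. Yet 10.2 also says the DSMB "will submit all SAEs to the independent statistician for review", and 14.1 gives the DSMB the task of "investigating AEs, and determining whether a reported AE relates to the intervention".

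**Analysis.** SAP section 7: "The primary analysis will be the ITT principle between the assigned treatment groups". Then: "The proportion of SAEs between the two groups will be analyzed via generalized estimating equations". It names no link function or model terms, has no rule for placing an event in a period or in the washout, and plans nothing for non-serious AEs or intolerance.

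**The concern.** A sham control allows excess events to be counted without anyone deciding what caused them. That works only if events are recorded alike in both conditions and the comparison is between the conditions. Here the recording sentence applies a causality opinion first, intolerance is worded around iTBS, and the commonest expected effects have no recording rule. The SAP then names groups that, in a crossover, may be the sequences rather than the treatments.

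At stake is whether the trial can report its own safety outcomes. An analysis can be re-specified before unblinding, but an event that was not recorded may not be recoverable.

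**Working it through.** The plan states no safety figure to reproduce. The 44 patients come from the CRS-R sample size (protocol 13.1, SAP 4) and are taken as given.

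**Step 1: set the sections side by side.**

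| Event | Stated outcome (10.1, SAP 2.2.4) | Recorded under 10.2 | Analysed in SAP 7 |
|---|---|---|---|
| SAE, relation not excluded | yes | yes, intervention phase | yes |
| SAE judged unrelated | yes | no by the collection sentence; yes if the DSMB sentence governs | only if captured |
| Intolerance under iTBS | yes | yes | no |
| Same discomfort under sham | yes, as an AE | unclear | no |
| Non-serious AE that settles unaided | yes | no rule; 14.1 presupposes reported AEs without saying which | no |

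Only the first row runs consistently from definition to analysis.

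**Step 2: what the assigned groups could mean.** Protocol section 5 randomises patients 1:1 to iTBS-first or sham-first, and every patient is due to receive both. Let s and i be the SAE probabilities under sham and iTBS. Without period or carry-over effects, the chance of any SAE is 1 − (1 − s)(1 − i) in each sequence, so the expected difference is zero however harmful iTBS is.

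The documents give no SAE rates, so the rates below are assumptions. The simulation used 5,000 trials, 22 patients per sequence, independent periods and full completion. Sequences were compared by Fisher's exact test, and treatments within patient by exact McNemar.

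| Assumed s / i | Any SAE, either sequence | Rejects by sequence | Rejects by treatment |
|---|---|---|---|
| 2% / 10% | 1 − 0.98 × 0.90 = 11.8% | 1.9% | 14% |
| 5% / 20% | 1 − 0.95 × 0.80 = 24% | 2.8% | 44% |
| 5% / 30% | 1 − 0.95 × 0.70 = 33.5% | 2.5% | 84% |

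The sequence comparison carries almost no information on iTBS versus sham.

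**Step 3: if treatment by period is meant.** There are two correlated binary outcomes per patient, which GEE clustered on patient suits. The remaining risk is an empty cell. With equal rate r and independent conditions, P(no events in 44) = (1 − r)^44, and P(at least one condition has none) = 1 − [1 − (1 − r)^44]².

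| Assumed r | (1 − r)^44 | At least one condition with zero |
|---|---|---|
| 1% | 0.643 | 87% |
| 2% | 0.411 | 65% |
| 5% | 0.105 | 20% |
| 10% | 0.010 | 2% |

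A log-odds contrast has no finite estimate when one condition has zero events.

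**Step 4: what zero events would show.** The exact two-sided 95% upper bound is 1 − 0.025^(1/44) = 8.0%. With the planned 15% dropout, 44 × 0.85 gives about 37 patients, and the bound is 1 − 0.025^(1/37) = 9.5%.

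**The case against.** **Capture may be wider than the collection sentence.** A reader might infer that unrelated SAEs and ordinary AEs are certain to go unrecorded. The documents do not support that. Section 10.2 has the DSMB monitoring all SAEs and passing them on, 14.1 has it judging AEs, and 14.3 has the principal investigator reviewing SAEs after every four randomised patients. If the DSMB decides relatedness, events must reach it first. This stands: for SAEs the fault is a contradiction, not a settled exclusion. But the events that 10.2 sends to the DSMB within 24 hours are the filtered ones, and no section read says which AEs are reported. The text of protocol section 12, which covers the DSMB, was not available for this check. A wider rule there would still have to be aligned with 10.2.

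**The groups may be the treatments.** SAP 2.2.1 and 4 use the word groups for the iTBS and sham conditions, and GEE has little purpose with one result per patient. This is a fair reading, so it would be wrong to say that no safety contrast can be obtained. The point is that SAP 7 does not say which reading applies, and one of them is uninformative.

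**GEE is not unestimable as such.** The empty-cell failure belongs to a logit link, which the SAP does not name. For 2 of 44 against 0 of 44, an identity link gives a finite risk difference of 2/44 = 4.5% (SE √(0.0455 × 0.9545/44) = 3.1%). Nor does an exact paired test rescue sparse data: McNemar gives 2 × 0.5² = 0.50 for 2 against 0, and 2 × 0.5⁵ = 0.0625 for 5 against 0. It also drops incomplete pairs. Replacing GEE is therefore a preference, not a correction.

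**Bias between conditions is not shown.** Attending physicians, nurses and raters are blinded (protocol 4.1). The causality filter mainly loses events; a reader who infers differential bias goes beyond the documents.

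**Rates could be higher.** These are severely brain-injured inpatients, and all-cause recording would raise counts. At an assumed 10% the empty-cell problem nearly vanishes.

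**Conclusion.** The point holds as a mismatch between stated outcomes, collection and analysis, and it should be corrected. Followed as written, the plan does not capture non-serious AEs short of intolerance, filters SAEs by causality opinion before the sham comparison, and analyses neither AEs nor intolerance. Conflicting sentences in 10.2 and 14.1 soften the SAE part but leave staff without one rule to follow.

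The size of the collection gap cannot be computed, because the documents give no event rates. The size of the analysis problem depends on the reading. By sequence, rejection stays at 1.9% to 2.8% even where iTBS raises the assumed SAE rate four- to sixfold. By treatment, the contrast is obtainable and GEE is acceptable, subject to the empty-cell risk of 87% down to 2% over assumed rates of 1% to 10%. These figures assume independent conditions and no dropout. The CRS-R primary analysis is not affected.

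**What to change.** **Protocol 10.2.** Record all AEs and SAEs in both conditions whatever their presumed cause, from the first session to the last assessment of period 2, washout included, with causality as a field on the form. Word intolerance so that it applies equally under sham. Reconcile 10.1, 10.2 and 14.1 so that one reporting rule governs.

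**SAP 7.** Define the comparison as iTBS versus sham by treatment received in the period of onset, and reconcile this with the ITT sentence. State in advance how washout events are attributed. Report AEs, intolerance and SAEs as counts and risk differences with 95% confidence intervals. GEE clustered on patient may stay if its link and its treatment and period terms are stated, with an exact or descriptive fallback for zero counts that includes the upper bound.

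**Cost.** A protocol amendment, a revised SAP paragraph and some extra CRF entry. The added burden should be small, since CRS-R is already assessed before and after every session.

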### **10.3 Follow up**

SAEs that cannot be excluded as attributable to the intervention under investigation will be monitored until resolution or stabilization. Participants who experience ongoing SAEs at the time of study termination will undergo further follow-up until recovery or stabilization of the condition post-termination.

## **11 END OF THE TRIAL AND WITHDRAWAL RULES**

### **11.1 Definition of end of the trial**

The end of the trial will be the completion of the last visit for the last participant.

### **11.2 Rules for withdrawal of participants**

The participation of individuals in either group should be discontinued if any of the following occur:

- SAEs, as determined by the DSMB, are deemed to be probably related to the trial protocol.
- The investigator believes that it is in the subject's best interest to withdraw from the trial.
- The legal representative of the patient chooses to withdraw consent for participation in the study.

## 13 STATISTICAL CONSIDERATIONS

### 13.1 Determination of Sample Size

We determined that enrolling 44 patients would provide 90% power to detect a mean difference of 1.2 points (standard deviation [SD] = 1.5) in CRS-R changes between the active and sham stimulation groups, using a two-sided  $\alpha$  of 0.05 and accounting for a 15% dropout rate. The anticipated  $1.2 \pm 1.5$ -point difference was conservatively estimated based on previous studies.

